## Data management

### Source data and documents

When a participant is enrolled, their information will be captured onto a participant recruitment form, which will allocate a unique participant identification number to the patient. Subsequent data collection will use this study number to identify the patient and record timing and clinical details onto the trial data collection form. Standardised data entry procedures will be followed across all sites to ensure consistency, with range and logic checks applied during entry to minimise errors. Key variables may be subject to independent verification to ensure data accuracy.

Once the patient has recovered from their critical illness, consent for their inclusion in the trial will be obtained by a suitable representative of the local hospital research team. Personal data will be stored on Excel spreadsheets saved on secure, password-protected servers within the RUH and on encrypted RUH laptops. Each trial site will have its own unique participant recruitment and trial data forms, with each research team able to access forms relevant to their participating site only. Clinical teams will have access only to data entry forms and will not be able to review patient data.

Any information that is analysed or transferred outside the clinical trial sites will be anonymised. Paper copies of any study documents, including consent forms and clinical letters with personal identifiable data, will be stored in a locked filing cabinet in an access-controlled area. Participant details will be anonymised in any publications that result from the study. Source data for this study will include certified scanned copies and/or paper copies of the consent form designed specifically for the study. An audit trail will be maintained for any changes to source data or electronic records, including time, date, and reason for the modification.

Patient notes will not be accessed by any member of staff outside of those involved in the direct care team until consent for this access has been obtained. Should the participant not survive their acute illness, only data collected for the primary outcome of the study will be used.

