## Study design, aims, and objectives

### Aim

To determine the change in total staff time required for repositioning proned patients using the BathMat and to assess the safety of use when compared with standard care.

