### Data collection by research team

A representative from the research team will review participants in the trial whilst the participant is in ICU throughout the period they are being proned, or the first working day afterwards if this has occurred over the weekend; once they have regained capacity; and at 3 months post discharge. They will collect patient data as detailed in Tables 4, 5 and 6 including standardised risk scoring measures used in ICU with potential relevance to our study (Waterlow, SOFA scores) [8, 9]. Data on device metrics will be obtained through discussion with clinical staff caring for the proned patient. They will ensure complete data sets are recorded through access to the clinical data entry form and spreadsheet, collect personal and nominated consultee opinions as required, and obtain patient consent. Patient notes will not be accessed by members of staff outside of those in the direct team until consent has been obtained.

**Table 4 Tab4:** Data to be collected by local research team—demographics

Patient metrics: Age, height, weight Frailty score Sequential Organ Failure Assessment (SOFA) [9] score on day 1 of proning Waterlow Pressure Ulcer Risk Assessment Scale on day 1 of proning [8] Pre-existing complications before day 1 of proning—see Table 6 ICU pressure sore risk score Medical comorbidities Diagnosis Device metrics—see Table 5 Proning complications—see Table 6

**Table 5 Tab5:** Data to be collected by local research team—device metrics (where clinical team who have used device are available)

Ease of introduction under the patient Ease of inflation/deflation Suitability of speed of inflation/deflation Ease of repositioning—head/arms Manual handling issue/concern Other comments

**Table 6 Tab6:** Data to be collected by local research team—proning complications

Pressure sore (face/chest/pelvis/knees/feet) Nerve injury (neck/arm/abdomen/leg) Blood vessel injury Skin abrasion Organ injury (liver/pancreas/genitals/ocular) Other	

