#### Nominated consultee opinion

In the situation where the patient has died, a nominated consultee will be appointed. The nominated consultee may include an independent mental capacity advocate appointed by the NHS Hospital Trust or an independent doctor (i.e. not involved in the trial). The opinion of the nominated consultee will be sought in the same manner as for the personal consultee. A nominated consultee will also be approached in the rare situations where no personal consultee is available (or one is available, but does not wish to be consulted). Upon the patient’s recovery, the patient will be approached directly for informed deferred consent. The patient’s decision will be final and will supersede the nominated consultee, where there is disagreement.

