#### Refusal or withdrawal of consent

If a patient declines informed deferred consent, or a consultee advises that they believe the patient would not choose to participate in the trial, and if a patient or their consultee (personal or nominated) withdraws consent/opinion at any time during the trial—this decision will be respected and will be abided by. All data up to the point of this decision will be retained in the trial, unless the patient or consultee requests otherwise.

For patients who decline informed deferred consent, or a consultee advises that they believe the patient would not choose to participate in the trial, but do not request removal of all data, the site will enter minimal pseudonymised data required for the primary outcome only. The justification for this is that as deceased patients cannot refuse consent to continue in the trial, excluding primary outcome data from the cohort of patients who survive to decline informed deferred consent would introduce substantial bias and impact upon the safety monitoring/reporting and, ultimately, the scientific validity of the trial and may prevent evidence of significant clinical benefit from being detected. No patient identifiable data will be recorded, and no further contact with the patient/consultee about the trial will be required.

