### Safety

Adverse event (AE) reporting will follow Health Research Authority guidance on safety reporting/Medical Devices (MEDDEV) guidance (https://ec.europa.eu/docsroom/documents/16477/attachments/1/translations).

Severity and causality of each with use of the device as per the above guidance. Adverse events and device deficiencies will be recorded by the research or clinical team and reported directly to the site principal investigator using the adverse event reporting form available here as a supplementary document at the above link and available here: https://ec.europa.eu/docsroom/documents/16477/attachments/2/translations. AEs identified in Tables 3 and 5 will be recorded daily by the research team whilst the participant remains within the trial.

An event assessed as ‘severe’ or ‘life-threatening’ will be considered a serious adverse event (SAE) in this trial. Considering that all eligible patients are critically ill and at increased risk of experiencing multiple AEs due to the complexity and severity of their condition, unexpected adverse events are only recorded if they meet the criteria for an SAE and are considered to have occurred as a consequence of the trial itself (i.e. deemed to be ‘possibly’, ‘probably’, or ‘definitely’ related to the trial procedures). Any SAEs, or device deficiencies that would have led to an SAE had suitable action not been taken, intervention not been made, or circumstances been less fortunate, will be reported by the sponsor of the clinical investigation to the UK National Competent Authority, using the standard MEDDEV SAE reporting form and summary tabulation immediately, or at most within the timelines laid out in the above guidance.

Staff members involved in the care of patients enrolled in the study will have the ability to report any concerns regarding adverse device effects and device deficiencies locally to the CI or directly to the central trial group via email contacts displayed at each trial centre.

Any concerns raised by trial teams at each centre, or the Trial Management Group, may result in a pause in the trial data collection pending formal review. This could include the formation of a formal Data Monitoring Ethics Committee.

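### Repositioning incidents in patients who die are left out of the safety summary, which leaves the safety result open to survivor-selection bias

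*Protocol article*

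**What the plan says.** The aim (Study design, aims, and objectives) is to determine the change in staff time and "to assess the safety of use when compared with standard care". Table 1 makes staff number and repositioning time the primary outcome. Minor and major adverse incidents during repositioning, such as line or tube displacement, are secondary outcome b.

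On whose data are used:

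- **Patients who die** (Source data and documents): "Should the participant not survive their acute illness, only data collected for the primary outcome of the study will be used".
- **Consent route after death** (Nominated consultee opinion): "In the situation where the patient has died, a nominated consultee will be appointed". The opinion is sought in the same way as from a personal consultee.
- **Patients who decline** (Refusal or withdrawal of consent): first, "All data up to the point of this decision will be retained in the trial, unless the patient or consultee requests otherwise"; then, for those who decline without asking for removal, "the site will enter minimal pseudonymised data required for the primary outcome only".

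On what is recorded: Table 3 complications are entered by bedside staff after each repositioning, on the same form as the primary outcome, under the study number only (Training in use of device; Data entry by clinical team). The Safety section adds: "AEs identified in Tables 3 and 5 will be recorded daily by the research team whilst the participant remains within the trial". Table 5 holds device usability items. Pressure sores and nerve, vessel and organ injuries are in Table 6.

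**The concern.** The rule for non-survivors conditions the safety summary on survival, which happens after repositioning and may be affected by the incidents being counted. A tube displacement followed by death would be recorded, and reported if serious and related, but would be absent from the tabulated comparison of incidents between methods.

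Secondary outcomes are reported descriptively, and the Statistical analysis section says the findings will inform safety, performance claims, regulatory planning and the design of a larger trial. Absolute incident rates are therefore a main safety product of this trial, and they are the quantity most exposed to a survivors-only rule.

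The rule also fits poorly with the rest of the document. A consultee is appointed for patients who have died, yet little beyond staff-time data could then be used. The Table 3 items need no access to notes, because they sit on the pseudonymised bedside form.

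**Working it through.** **Inputs.** Sample size 30 (Sample size). Line or tube displacement in up to 12.5% of proned patients (Background and rationale), taken here as a ceiling for the event rate p. Mortality m is not given, so 20–50% is shown as an assumption. The plan gives no figure of its own for safety, so there is none to reproduce.

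**Step 1: patients and events expected.** With all patients used, 30 × 0.125 = 3.75 patients with a displacement. Under the survivors-only rule, 30m patients leave.

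**Step 2: what survivors show.** If death is unrelated to events, 3.75 × (1 − m) patients with an event remain and the rate stays at 12.5%. If an event doubles the risk of death, mortality without an event is m0 = m / (1 − p + 2p) = m / 1.125, and with an event m1 = 2 × m0. The patients with an event who remain number 3.75 × (1 − m1), and the apparent rate is that number divided by 30(1 − m).

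For m = 40%: m0 = 0.40 / 1.125 = 0.356 and m1 = 0.711. Then 3.75 × 0.289 = 1.08 remain, and 1.08 / 18 = 6.0%.

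The last column compares 12.5% with an illustrative 6.25% under the other method (true difference −6.25 points), with the same m0 and m1 for both. The survivor rate for each is p(1 − m1) / [p(1 − m1) + (1 − p)(1 − m0)].

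| Assumed mortality | Patients leaving | Events left, unrelated to death | Events left, risk doubled | Apparent rate, risk doubled | Apparent difference (points) |
|---|---|---|---|---|---|
| 20% | 6 | 3.00 | 2.42 | 10.1% | −5.1 |
| 30% | 9 | 2.625 | 1.75 | 8.3% | −4.3 |
| 40% | 12 | 2.25 | 1.08 | 6.0% | −3.1 |
| 50% | 15 | 1.875 | 0.42 | 2.8% | −1.5 |

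**Step 3: contrast between methods.** In every row the odds ratio stays at its true value of 0.467, because the event–death link is the same under both methods. If instead events are equally frequent (true risk ratio 1) but double the risk of death under one method only, survivor rates at 30% baseline mortality are 12.5% and 0.125 × 0.4 / (0.125 × 0.4 + 0.875 × 0.7) = 7.5%, a ratio of 0.60. At 20% and 40% baseline mortality the ratio is 0.77 and 0.36. Which method would look better depends on where the stronger link lies, and the documents do not say.

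**Step 4: precision alone.** With zero events, the one-sided 95% upper limit is 1 − 0.05^(1/n): 9.5% for n = 30, 13.3% for n = 21 and 18.1% for n = 15 (all patients, 30% and 50% mortality). These describe lost precision in one pooled proportion, not bias between methods.

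Steps 2 and 3 treat each patient as contributing to one method. A patient with two or more sessions loses data under both, which tempers the contrast. The sample-size section assumes a dropout of one third after the first session, so about 30 × 1/3 = 10 patients would contribute to one method only.

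**The case against.** The rule limits what is used, not what is recorded. Bedside entry of Table 3 items, adverse-event recording and reporting of serious events to the competent authority do not depend on survival. A reader might infer that safety data from patients who die are discarded, or that a fatal device event would go unnoticed. The document does not support that. This part of the objection stands.

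Nor is bias in the comparison demonstrated. Safety is descriptive, a common event–death link leaves the odds ratio unchanged, and no link means no bias. This also stands, and it limits the point to exposure to bias.

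Three further inferences should be set aside:

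- The wrong table number does not bias anything. Data collection by research team separately provides for Table 6, so this is a cross-reference error.
- The statement that excluding data "would introduce substantial bias and impact upon the safety monitoring/reporting" concerns primary-outcome data of survivors who decline. It is not the protocol arguing against its own rule for the dead.
- The restriction "Patient notes will not be accessed by members of staff outside of those in the direct team until consent has been obtained" does not shut down adverse-event recording. The Safety section allows recording by the research or clinical team, bedside staff enter Table 3 events, and consultee opinion is sought ideally within 24–48 h of randomisation.

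The two sentences on patients who decline might also be reconciled by reading the second as what is entered after refusal. That is possible but not stated, so the wording needs clarifying.

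The objection does not remove the sentence on non-survivors. It is an explicit rule, and an analysis plan that follows it cannot use their incidents.

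**Conclusion.** The point holds in this form: as written, repositioning incidents of participants who die are excluded from the safety summary, although they are recorded and although comparative safety is part of the aim. The safety result is therefore open to survivor-selection bias.

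The size rests on assumptions. At 30–50% mortality, 9–15 of 30 patients leave the safety set. If an event also doubles the risk of death, a true 12.5% rate would appear as 8.3% to 2.8% over that range. If death is unrelated to events, the cost is precision alone. Distortion between methods needs a link that differs by method, and its direction is unknown.

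This should be fixed, but it does not threaten the trial's main result: the staff-time data of patients who die are kept.

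**What to change.** 1. Amend the sentence on non-survivors in Source data and documents. Table 3 complications and recorded adverse events and serious adverse events from all randomised participants, including those who die, should be used in the safety summary. Table 6 data from those who die should be used where the nominated consultee's opinion allows. Removal requests are respected throughout.
2. Reconcile the two sentences in Refusal or withdrawal of consent on what is kept for those who decline. How far this may go beyond the minimal set is for the ethics committee.
3. In the Safety section, correct Tables 3 and 5 to Tables 3 and 6.

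The cost is an ethics-approved wording amendment. No visits are added, and the Table 3 items are already on the bedside form. Recruitment is expected to run to about July 2026, and the change should be in place before analysis.

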### Data handling and record keeping

Data will be collected and retained in accordance with the UK Data Protection Act 2018 and UK General Data Protection Regulation (GDPR). For this study, research data will be kept for at least 10 years. Personal data (e.g. name and address, or any data from which a participant might be identified) will not be kept for longer than is required for the purpose for which it has been acquired. Procedures will be in place to monitor data completeness and validity, and any discrepancies will be followed up with the local research team.

### Access to data

For monitoring purposes, the CI will allow persons responsible for the audit, representatives of the REC, and other regulatory authorities to have direct access to source data/documents. The trial manager (in collaboration with the CI) will manage access rights to the data set. Prospective new users must demonstrate compliance with legal, data protection, and ethical guidelines before any data are released.

Patient identifiable data (containing name, date of birth, patient identification number) will only be accessible by clinical members of the research team to allow further data collection pre-publication, if required. Pseudo-anonymised data will be shared with the non-clinical members of the research team named as study contacts in this document for the purposes of statistical, mechanical engineering, and health economic analysis. These data will identify participants by their study number only. Role-based access controls and password protection will be applied to all electronic datasets.

### Archiving

The RUH Bath NHS Foundation Trust is the data custodian for this study. All research data will be retained in a secure location during the conduct of the study and for at least 10 years after the end of the study, when all paper records will be destroyed by confidential means. An archiving plan will be developed for all study materials in accordance with RUH Standard Operating Procedures. Individual sites will archive their site files, consent forms, and related documents (paper and electronic) according to their hospital archiving policies.

### Access to the final study data set

Members of the Trial Management Group (TMG) will develop a data sharing policy that is consistent with the RUH Bath NHS Foundation Trust and University of Bath policies. It is anticipated that anonymised study data will be kept for future analysis and may be shared with other researchers, including those outside of the UK, European Union (EU), and European Economic Area (EEA), to enable international prospective meta-analyses.

The final study data set will be stored as restricted data on the RUH’s research data repository. Data will be made available to approved bona fide researchers only after their host institution has signed a data sharing agreement, which will be issued by the Research and Development (R&D) department and confirmed by the CI or appointed delegate. Details of how to request access will be available at the RUH R&D website.

### Monitoring of the final study dataset

The data collected for primary and secondary outcomes will be stored on NHS servers as a Microsoft form/Microsoft Excel spreadsheet. This will be backed up twice weekly to minimise any risk of data loss. Data entered will be reviewed by the CI or trial manager, and any concerns regarding data validation will be raised with local study teams for further assessment and consideration of any remedial actions required.

### Study management

The CI will take overall responsibility for managing the various components of the study, with the support of the trial manager(s) and will meet regularly (as required) with the leads for each component and PIs for each research site.

### Trial Management Group

The TMG will have responsibility for the day-to-day management of the study. The TMG will comprise the CI, all co-investigators, the trial manager, and other key study staff. The TMG will meet on a regular basis with a core working group of staff having weekly progress meetings.

### Trial Steering Committee (TSC)

The TSC will have oversight of the study and will meet every 3 months throughout the study to review progress and provide guidance on future plans. The Trial Steering Committee will be responsible for overall supervision on behalf of the sponsor and funder and will ensure that it is conducted in accordance with the relevant guidelines and regulations.

It will consist of the Chair ([name]), voting members ([name], [name], [name], [name], [name], [name]), and observers ([name], [name], [name], [name]), with additional observers attending as required at the request of the Chair.

### Patient and public involvement (PPI)

Before data collection, a PPI group has been recruited and convened to review the trial design, device, and consenting process. Their feedback has been used to update the device and protocols as required.

During data collection, leaflets and posters will be available to recruitment sites with information for patients, families, and staff, with details on how to get more information about the device and trial through our project website, and to contact the study team with questions. Anyone making contact will be offered the opportunity to receive monthly updates about the project. The PPI team leader recruited prior to this trial will also sit on regular steering group meetings, providing regular updates to the team on PPI input on the device.

## Monitoring, audit, and inspection

### Monitoring

The study will be overseen by the Trial Steering Group and the Trial Management Committee, with a central monitoring plan agreed in advance of trial commencement. Oversight will focus on enrolment progress, protocol adherence, and intervention fidelity. Recruitment rates will be reviewed on a regular basis using site enrolment logs and central screening logs. Any site not meeting expected enrolment targets will be supported through targeted engagement, additional training, and reclarification of eligibility or consent procedures as appropriate. Regular communication with sites will ensure that any local barriers to recruitment are identified early and addressed promptly to protect trial timelines.

To support consistent delivery of the intervention, the central research team will implement structured training for all personnel involved in trial delivery. This training will be accompanied by clear procedural documentation and checklists. Adherence to the intervention protocol will be assessed using routinely collected trial data. The research team will review these data regularly to assess consistency across sites, including confirmation that the intervention was delivered in accordance with the planned sequence and within appropriate timeframes. Any deviation from the expected protocol will be recorded and reported to the trial manager and chief investigator, and if systematic, investigated and addressed through direct engagement with site teams.

Auditing of the trial will be conducted in accordance with the agreed monitoring plan. The NIHR will oversee trial conduct through regular review of progress, documentation, and reported deviations. Audits or inspections by the Research Ethics Committee or other regulatory bodies will be undertaken if required. The process for audit is independent of the sponsor and investigators and will be managed through NIHR oversight structures, which include personnel with extensive experience in the conduct and evaluation of clinical trials. All documentation will be available for inspection as required.

